### Functional outcomes

The Kujala score is a 13-item questionnaire used to evaluate subjective symptoms and functional limitations in patients with PFP [29]. Kujala grade ranges from 0 to 100, with 100 reflecting no signs of PFP. This index shows high validity and is responsive to change [28]. To detect improvement, a change of 8–10 points is required [28].

The International Knee Documentation Committee (IKDC) ‘Subjective Knee Form’ is a tool containing 11 items: 7 on knee symptoms, 2 on function, and 2 on sports activities, resulting in a score ranging from 0 to 100, with 100 reflecting the highest level of pain and functional restrictions. The IKDC has been validated in people with PFP [30]. The IKDC showed high internal consistency (0.92) and test-retest reliability (0.95), with a value change of 9 points indicating true change [31].

### Activity level

The Tegner activity score consists of 1 item, which scores the level of work- and sport activities on a 10-point scale, with 10 reflecting a high level of activity [32].

### Quality of life

The health-related quality of life (EQ-5D-5 L) questionnaire consists of 5 dimensions (mobility, self-care, usual activities, pain/discomfort, and anxiety/depression) that are scored on 5 levels (no problems, slight problems, moderate problems, severe problems, and extreme problems) [33]. An index value will be calculated to reflect health status on a scale of 0 to 1, where 1 represents maximum quality of life.

### Functional ROM

The maximum pain-free flexion angle (MPFFA) is measured by the DSDT, which was performed according to the instructions mentioned elsewhere [34]. The DSDT is a reliable and valid performance test simulating stair descent with almost perfect intra- and interobserver reliability (*ICC* 0.83–0.85) and an average positive correlation between the DSDT score and the total AKPS score (*r*_*s*_ = 0.31, *p* = .030) [34].

#### Other study parameters

This study will include items strongly recommended by the International Patellofemoral Research Network (iPFRN) in the REPORT-PFP consensus statement [35]. These include demographics, such as age, biological sex, symptom duration, and unilateral/bilateral symptoms [35]. Furthermore, physical examination data, such as height and weight (and hence BMI) will be recorded. To evaluate the adherence to the PT, patients will also receive a weekly email during the PT asking how often they have visited the physiotherapist and how often they have executed the PT at home.

Any adverse events (AEs) will be monitored, as explained in the ‘Adverse event reporting and harms’ section. The rate of ROH after surgery will be registered as a separate outcome.

### Participant timeline

Figure 1 provides an overview of the study design and procedures.

**Fig. 1 Fig1:**
[figure not shown]
Flowchart of the study protocol and procedures

### Sample size

Our primary outcome is the between-group difference in overall knee pain 12 weeks after PT and 18 weeks after TTT and PT, measured with the VAS score. Our hypothesis is that the improvement in the TTT group will be greater than the improvement in the PT group.

To detect the superiority of the treat-to-target TTT with PT to PT alone, we calculated the required sample size for an independent samples t-test on the following assumptions: power (1-beta) 0.8, significance level (alpha) 0.05, and two-sided testing. Effect size was set at the MCID for VAS-pain, based on a study by Crossley et al., who demonstrated that a change in the VAS score of two points or more is considered clinically relevant and worthwhile for performing surgery [28]. Based on a study by Bayoumi et al., which compared different surgical techniques for patellar maltracking without instability, the anticipated mean for the PT only group was 6.2 (reflecting the pre-operative value), and SD was 2.0 [17]. Based on these parameters, a sample size of 16 patients per group is needed. Anticipating on a loss to follow-up of 20%, 20 patients per group are needed.

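### The figure of 16 per group is a normal-approximation result; the independent-samples t-test named in the sizing has 78.1% power at 16 and needs 17 for 80%, a minor misstatement

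*Protocol article*

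**What the plan says.** The Sample size section names the test and the error rates: "we calculated the required sample size for an independent samples t-test on the following assumptions: power (1-beta) 0.8", with "significance level (alpha) 0.05, and two-sided testing". The effect is set at the minimal clinically important difference for VAS pain, on the ground that "a change in the VAS score of two points or more is considered clinically relevant". For the comparison arm, "the anticipated mean for the PT only group was 6.2 (reflecting the pre-operative value), and SD was 2.0".

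From these inputs the section concludes: "Based on these parameters, a sample size of 16 patients per group is needed". It then allows for attrition: "Anticipating on a loss to follow-up of 20%, 20 patients per group are needed".

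The section does not say which formula was used. Under Statistical methods, Primary endpoint, the primary analysis is a multivariable linear regression with baseline VAS and sex alongside treatment group. Its outcome is the mean of two VAS scores taken at the end of the physiotherapy programme.

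**The concern.** A t-test estimates the SD from the data and pays for this with a larger critical value. With about 16 patients per group that cost is large enough to change the answer by one patient. A calculation that names the t-test but uses the normal distribution will therefore state slightly more power than the test has.

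Rounding gives no cushion at the planned loss. 16 / 0.8 is exactly 20, so 20% attrition leaves exactly 16 per group. If 16 is one short for the named test, the 80% attached to it is wrong as written. What is at stake is the accuracy of a published power statement, not the viability of the design.

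**Working it through.** **Inputs** (all from the Sample size section unless noted)

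- Difference in means: 2 VAS points
- SD: 2.0, so the standardised difference is d = 2 / 2.0 = 1.0
- Two-sided alpha 0.05, power 0.80
- Allocation 1:1 (Randomisation section)
- Loss to follow-up 20%

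**Step 1. Reproduce the stated figures.** The normal-approximation formula is

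n per group = 2 × (z₀.₉₇₅ + z₀.₈₀)² / d² = 2 × (1.960 + 0.842)² / 1² = 15.70, rounded up to 16.

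Inflation for loss: 16 / (1 − 0.20) = 20. Both stated figures are reproduced. On this approximation the power at 16 per group is 80.7%.

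**Step 2. Apply the named test.** For a two-sample t-test, power comes from the noncentral t distribution with df = 2n − 2 and noncentrality d × √(n/2). At n = 16, df = 30, the noncentrality is √8 = 2.828 and the two-sided critical value is 2.042 rather than 1.960.

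| Evaluable per group | Loss from 20 | Power of unadjusted t-test |
|---|---|---|
| 16 | 20% | 78.1% |
| 17 | 15% | 80.7% |
| 20 | 0% | 86.9% |

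The smallest n reaching 80% is 17. The shortfall at 16 is 80 − 78.1 = 1.9 points.

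**Step 3. Look at the planned analysis.** The regression has four parameters (intercept, treatment, baseline VAS, sex), so with 32 evaluable patients df = 32 − 4 = 28. If the baseline-outcome correlation is r and sex explains nothing further, the residual SD is 2.0 × √(1 − r²), and the effective standardised difference is 1 / √(1 − r²). The article gives no r, so the range below is an assumption.

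| Assumed r | Power at 16 per group |
|---|---|
| 0 | 77.9% |
| 0.2 | 79.6% |
| 0.23 | 80.1% |
| 0.3 | 81.6% |
| 0.5 | 88.3% |

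Power crosses 80% at about r = 0.23.

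**The case against.** The case for leaving the sentence alone has four parts.

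- **The figures reproduce.** The normal-approximation formula is in common use for comparing two means, and 16 and 20 follow from it exactly. This is true. But the section attaches its figure to a t-test, and for that test the figure is one short.
- **The inputs are coarser than the gap.** The SD is given to one decimal. An SD of 1.95 gives 80.2% t-test power at 16 per group, and 2.04 gives 76.5%. This stands as a reason not to make much of the 1.9 points. It does not make 16 right for the stated SD of 2.0.
- **The trial will not be analysed by an unadjusted t-test on one reading.** Baseline adjustment recovers the shortfall at a modest correlation. Averaging two VAS scores may do the same: if SD 2.0 describes a single reading and the two readings correlate at 0.9 (both assumptions), t-test power at 16 per group is 80.2%. This stands, and it limits the point to the wording of the sizing.
- **Sizing on an unadjusted test and analysing with adjustment is accepted practice.** It is usually conservative, and claiming no credit for an unknown correlation is not an error. At r = 0 the two extra parameters cost only 0.2 points (77.9% against 78.1%). This stands in full.

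A reader might also infer that the trial is underpowered, that it has no margin, or that it should recruit 22 per group, since 17 / 0.8 = 21.25. The documents do not support these readings. Twenty per group gives 86.9% with no loss and still exceeds 80% at 15% loss, even for the unadjusted test, and the planned regression needs only a modest baseline correlation to reach 80% at the full 20% loss.

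**Conclusion.** The point holds as a minor correction to a stated number. For the inputs and the test that the section names, 16 evaluable patients per group gives 78.1% power, not 80%, and 17 are needed. This follows from the article's own figures and needs no outside assumption beyond the usual t-test conditions (normal outcome, equal SD in both groups).

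The error is confined to the unadjusted t-test at the full 20% loss. Whether the planned regression falls short at that loss cannot be settled from the article, because it depends on a baseline-outcome correlation that is not given. Below about 0.23 the regression would be short by at most 2.1 points (80 − 77.9); above it there is no shortfall. That is not a material power deficit, and it gives no reason to change the design.

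**What to change.** Keep 20 per group and restate the power in the Sample size section, for example:

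*Sixteen evaluable patients per group gives about 78% power for the unadjusted t-test; 80% requires 17 per group, that is, at most 15% loss, and with no loss the power is 87%. The planned regression adjusted for baseline VAS and sex reaches 80% with 16 per group if the baseline-outcome correlation is about 0.23 or more (an assumption).*

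This costs one restated passage. The stated power becomes slightly less favourable. Recruitment, the loss allowance and the analysis are unchanged.

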### Feasibility of recruitment

Given the > 50 TTTs for patients with chronic PFP already performed annually in the CWZ, and accounting for patients who are not willing to participate, we expect to have sufficient numbers of patients for our inclusion within 24 months. The CWZ is a nationally recognized top clinical expertise centre in (patellofemoral) knee surgery and performs approximately 80% of patellofemoral surgeries in the Netherlands, including TTT [36].

### Data collection methods

Plans for assessment and collection of outcomes.

The clinical assessment data and PROMs data will be collected in CastorEDC. This data collection will be organized by the study coordinator.

Plans to promote participant retention and complete follow-up.

Participants will be closely monitored by the study coordinator to ensure follow-up. To reduce patient burden, data collection will be web-based as often as possible.

### Data management

We have created a data management plan in line with the General Data Protection Regulation, which can be viewed upon request. The data will be managed within the online CastorEDC system. This is a secure cloud-based platform that contains an audit trail, automatic range checks, and pseudomised study IDs for all data.

### Confidentiality

The type of data that is collected is in line with the General Data Protection Regulation. Study IDs are pseudonymised in CastorEDC for all data. The key to the study ID is safely kept by the study coordinator. The data will be stored for 15 years.

### Statistical methods for primary and secondary outcomes

In accordance with the iPFRN, the REPORT-PFP consensus statement outcome measure description will be adequate [35]. The items described in the assessment will be in adequate detail to allow replication. We will report *n* (%), the mean (SD), and median (interquartile range; IQR) for categorical/descriptive, normally distributed continuous and non-normally distributed continuous data, respectively [35]. Results over time will be visualized descriptively in spaghetti plots. The primary analyses will be performed following the intention-to-treat method.

Statistical analyses will be done using *R* software (R Foundation for Statistical Computing, Vienna, Austria).

#### Primary endpoint

The primary outcome parameter is the between-group difference in VAS score, at 12 weeks after start of the PT (week 18 for TTT group). For analysis of the primary parameter, the mean of the two VAS scores at 12 weeks of the PT in the TTT group will be compared with that of the PT group. Baseline VAS score, biological sex, and treatment group will be included as covariates in a multivariable linear regression analysis.

#### Secondary endpoints

For the secondary parameters (functional outcomes on the Kujala and IKDC score, activity level on Tegner score, QoL on the EuroQol-5D-5 L score, and functional ROM on the DSDT score) at 12 weeks after the start of the PT (week 18 for TTT group), the between-group difference will be assessed using multivariable linear regression analysis in the same manner as the primary endpoint.

To assess the longitudinal clinical effectiveness of both groups, linear mixed models for repeated measures (MMRM) will be used for the secondary outcomes and activity-related knee pain on VAS score during the PT from baseline to 12 months follow-up. MMRMs take the correlation of multiple measurements over time within one patient into account. In the MMRM, these secondary outcomes will be analysed as dependent variables. To evaluate the effect at different time points, the fixed effects will be patient, time, and the treatment group (TTT versus PT only). Time will be included as dummy variable, with baseline as reference.

The main effects for treatment will be reported as difference in means with 95% confidence intervals (CI).

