#### TTT and PT versus PT only

The study involves four outpatient visits (at inclusion/randomisation, 6 weeks after the start of the intervention, after 12 (PT group)/18 weeks (surgery + PT group), and after 26 weeks in both groups). A physical examination will take place at every outpatient visit, with the addition of the decline step-down test (DSDT) at baseline and 12/18 weeks after randomisation. Patients will complete online questionnaires at every outpatient visit and 12 months after randomisation.

After randomisation, patients will either have a TTT (treatment group) or start with the PT (control group). From 12 weeks, there will be the possibility to crossover from the PT group to surgery if the symptoms do not improve. The criteria for this are a persisting high level of pain and patient-reported lack of effect of the PT. In that case, surgery will be performed within 2 weeks. Participants will then follow the same protocol as the TTT group, including the PT programme, surveys, and physical measurements.

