### VAS

In the TTT group, it could be possible that the trajectory of recovery might affect VAS pain scores at week 18 still. Therefore, a secondary outcome is the between-group difference in VAS pain score over time, which enables us to assess whether the VAS score at 12/18 weeks is stable or changes over time. This will be from baseline to 12 months follow-up, also including the VAS pain score in the weekly questionnaire during the PT.

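### The longitudinal mixed model has no treatment-by-time term and counts baseline as an outcome time, so it gives no effect at any single visit and generally understates the treatment difference

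*Protocol article*

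**What the plan says.** The protocol article, in the statistical section *Secondary endpoints*, plans two analyses. The first is a regression at 12/18 weeks built like the primary one, with baseline as a covariate. The second is a mixed model for repeated measures, covering the secondary outcomes and "activity-related knee pain on VAS score during the PT from baseline to 12 months follow-up".

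Only the second is at issue. Its terms are given as "To evaluate the effect at different time points, the fixed effects will be patient, time, and the treatment group", followed by "Time will be included as dummy variable, with baseline as reference". No treatment-by-time term is listed. A closing line, not tied to either analysis, reads "The main effects for treatment will be reported as difference in means with 95% confidence intervals (CI".

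The section *VAS* gives the purpose of following pain longitudinally. Surgical recovery might still affect the week-18 score, so the group difference is traced to 12 months, "which enables us to assess whether the VAS score at 12/18 weeks is stable or changes over time". That section also brings in the weekly VAS scores collected during physiotherapy.

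**The concern.** A model with time and treatment as main effects only assumes the same TTT–PT difference at every time. The protocol itself gives reasons to expect otherwise:

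- At baseline the data are collected before randomisation, so the expected difference is zero.
- At 6 weeks the TTT patients are at or near the end of the splint phase, while the PT patients are halfway through their programme.
- From 12 weeks PT patients may cross over to surgery, which the Discussion accepts can affect longer-term comparisons.

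The single coefficient blends these periods. It cannot answer the question about individual time points that the same sentence sets, nor the question about stability. This is the only formal between-group analysis that the article describes beyond 12/18 weeks, and the only formal check on whether recovery from surgery still affects the week-18 pain score.

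**Working it through.** **Inputs from the protocol article**

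- Model terms, time coding and reported estimate: *Secondary endpoints*.
- Questionnaires: "Patients will complete online questionnaires at every outpatient visit and 12 months after randomisation". With four outpatient visits this gives T = 5 (baseline, 6, 12/18 and 26 weeks, 12 months).
- Decline step-down test (DSDT): baseline and 12/18 weeks, so T = 2 (*TTT and PT versus PT only*).
- VAS: the five times above plus weekly scores over 12 weeks of physiotherapy (*VAS*; *Strategies to improve adherence to interventions*), so T is about 17.
- Difference of 2 points and SD 2.0: *Sample size*.

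**Assumptions, not in the document:** balanced data; a random intercept (equal variances and correlations) unless stated otherwise; a true difference of 0 at baseline and 2 points at every later time. The last ignores crossover.

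**The plan's own figure.** The article gives none for the longitudinal model. The sample size that supplies the scale reproduces with the normal approximation: 2 × (1.96 + 0.84)² × (2.0/2)² = 15.7, so 16 per group, and 16/0.8 = 20. The t-test version gives 16.7, so 17; nothing below depends on this.

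**Step 1: what the treatment coefficient estimates.** With balanced data, categorical time and within-patient covariance S, it is a weighted mean of the differences d at each time, with weights w = S⁻¹1 / (1′S⁻¹1). Baseline receives one of these weights. Under a random intercept all weights are 1/T, so a constant later difference of 2 is reported as 2 × (T − 1)/T.

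| Outcome | T | Reported, if the true difference is 2 | Loss |
|---|---|---|---|
| Questionnaires | 5 | 2 × 4/5 = 1.60 | 20% |
| VAS with weekly scores | about 17 | 2 × 16/17 = 1.88 | 6% |
| VAS, week-6 difference also 0 | about 17 | 2 × 15/17 = 1.76 | 12% |
| DSDT | 2 | 2 × 1/2 = 1.00 | 50% |

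The questionnaires and DSDT are not on the VAS scale; for them only the percentage matters.

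**Step 2: sensitivity to the covariance.** Under AR(1) with correlation 0.7 and times treated as equally spaced, the baseline weight is 1/[2 + (T − 2) × 0.3]. For T = 5 that is 1/2.9 = 0.345, giving 2 × 0.655 = 1.31. For T = 17 it is 1/6.5 = 0.154, giving 2 × 0.846 = 1.69. If the baseline SD is 1.5 rather than 2.0, with a common correlation of 0.3 to 0.5, the five-time figure is 1.15 to 0.86.

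**Step 3: differences that vary over time.** For assumed differences of 0, +1, −2, −2 and −0.5 at the five times, the coefficient under a random intercept is −3.5/5 = −0.70, which is the difference at none of them.

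**Step 4: simulation.** In 300 simulated trials (16 per arm, five times, random intercept, true post-baseline difference −2), the additive model averaged −1.64 against −1.60 from the formula. With treatment-by-time terms the 12/18-week contrast averaged −2.04.

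**Step 5: patient as a fixed effect.** With 40 patients and five times, patient indicators (40), time (4) and treatment (1) make 45 columns of rank 44. Treatment is a sum of patient indicators, so its main effect is not estimable. Replacing it with four treatment-by-time columns gives 48 columns of rank 48, which is estimable.

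**The case against.** The strongest reply is that the sentence is loosely worded. Patient was presumably meant as a random effect, and if that is forgiven, the stated aim and the time dummies make an intended interaction plausible too. The article also condenses a fuller protocol. This shows that the authors may have meant the right model. It does not change what is written: the article commits to a list of terms, a time coding and a reported estimate, and together they do not serve the stated aim.

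The reply carries more weight on size and reach. A reader might infer that the longitudinal VAS result will be 20% or 40% too small, because five visits give (0 + 2 + 2 + 2 + 2)/5 = 1.6 cm, or (0 + 0 + 2 + 2 + 2)/5 = 1.2 cm with no week-6 difference. The documents do not support that for VAS, since the weekly scores enter the model and dilute the baseline contribution. Nor is the shrinkage certain: no covariance is stated, and a negative baseline weight is possible in theory if baseline is more variable than later scores and strongly correlated with them.

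A reader might also infer that the trial's main conclusion is at risk. It is not. The primary regression and the 12/18-week secondary regressions adjust for baseline and give a proper estimate at the key time. Spaghetti plots are planned as well, though they are descriptive only.

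**Conclusion.** The point holds for the longitudinal secondary analyses and should be fixed. Regardless of any numerical assumption, the listed terms yield no visit-specific effect and cannot show whether the 12/18-week VAS difference is stable. The pull toward zero is the general tendency. Under balanced data, a random intercept and a constant post-baseline effect it is about 20% for the questionnaires, about 6% for VAS (about 12% if the week-6 difference is also zero) and half for DSDT. Other plausible covariances make it larger: for the five-time case the calculated values run from 0.86 to 1.60 of a true 2. Read literally, with patient as a fixed effect, there is no estimable treatment main effect to report.

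**What to change.** In *Secondary endpoints*:

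- Make patient a random effect or the repeated-measures subject.
- Include categorical time and treatment-by-time.
- Handle baseline either as a covariate, with post-baseline times only as outcomes, or as a mean common to both arms.
- Report the treatment contrast with 95% CI at each scheduled time at which the outcome is measured: 6, 12/18 and 26 weeks and 12 months, plus the weekly physiotherapy times for VAS.
- Reword the sentence on main effects so that it covers only the 12/18-week regressions. Deleting it would remove reporting that is correct for them.

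This costs a few lines of text and code and needs no new data. The price is precision: an interval for one visit is wider than one for an average over all times. The change should be made before analysis, because altering the model afterwards in an unblinded trial would look post hoc.

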### Randomisation

Patients will be enrolled in the study by the study coordinator in the orthopaedic department. All patients who consent to participate in the study and meet the inclusion criteria will be randomised. Randomisation will be performed by the study coordinator after consent is signed and baseline data is collected. Patients will be randomised to the TTT + PT: PT only in a 1:1 ratio. The randomisation process will be carried out using a computer-generated randomisation method in the Castor electronic data capture (EDC) system [24], in random blocks of 4. The exact randomisation algorithm is unknown to any of the investigators; hence, concealment of allocation is successful in all patients.

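### The longitudinal model lists patient as a fixed effect beside treatment group, so the treatment main effect it promises to report is not identified

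*Protocol article*

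**What the plan says.** The article's section on secondary endpoints sets out two kinds of analysis. Secondary outcomes at 12/18 weeks get a regression like the primary one, with one value per patient. Change from baseline to 12 months, including activity-related pain on the VAS, gets a linear mixed model for repeated measures.

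For that second model the section says that "the fixed effects will be patient, time, and the treatment group (TTT versus PT only). Time will be included as dummy variable, with baseline as" the reference level. The quantity to be reported follows: "The main effects for treatment will be reported as difference in means with 95% confidence intervals (CI"). The same section describes the model class by saying that "MMRMs take the correlation of multiple measurements over time within one patient into account".

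No random effect, subject term, residual covariance structure or group-by-time term is named there or elsewhere in the article. The VAS section states the question as a between-arm one: "a secondary outcome is the between-group difference in VAS pain score over time". The arms are parallel: "Patients will be randomised to the TTT + PT: PT only in a 1:1 ratio".

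**The concern.** In a parallel-group trial analysed as randomised, treatment does not vary within a patient. Once every patient has a separate fixed intercept, those intercepts absorb all differences between patients, including the difference between the arms. Nothing is left from which to estimate a group main effect, yet that is the quantity the section says will be reported.

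The list also conflicts with the section's own description of the model. In a mixed model, within-patient correlation is represented by making patient a random effect or the subject of a residual covariance matrix. Putting patient among the fixed effects is a different model.

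At stake are the longitudinal between-arm results. The longitudinal VAS comparison matters most. The article relies on it to show whether the 12/18-week score is stable, because recovery from surgery may still affect pain at week 18 in the TTT arm.

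**Working it through.** **Inputs.** From the article: 20 patients per arm (Sample size); SD 2.0 on the VAS (Sample size); five questionnaire times, namely four outpatient visits including baseline plus 12 months (TTT and PT versus PT only); time as dummies with baseline as reference (Secondary endpoints). The intraclass correlation (ICC) is not given, so 0.3, 0.5 and 0.7 are assumed.

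**The plan's own figure.** The article gives no figure for the longitudinal model. Its sample size reproduces with the normal approximation: 2 × (1.96 + 0.84)² × 2.0² / 2² = 15.7, so 16 per group, and 16 / 0.8 = 20.

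**Rank of the model as listed.**
- Intercept + 39 patient dummies + 4 time dummies = 44 columns, rank 44.
- Adding group gives 45 columns, and the rank stays 44. The group column equals the sum of the indicators of the patients in that arm.
- With 16 per arm: 37 columns, rank 36.
- With two times only, as scheduled for the decline step-down test: 42 columns, rank 41.
- With group-by-time added (20 per arm, five times): 49 columns, rank 48. The four interaction terms can be estimated; the group main effect still cannot.
- With patient removed: 1 + 4 + 1 = 6 columns, rank 6. The group effect can be estimated.

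The weekly VAS scores add time dummies, which raise columns and rank equally, so the shortfall of one remains. None of this needs an assumption about variances.

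**What software does.** In R, a linear model with patient before group returns a missing group coefficient, and generalised least squares with compound symmetry stops as singular. If group comes before patient under reference coding, the last patient dummy is dropped instead. The group coefficient then has weight −1 on one patient, +1 on one patient in the other arm, and 0 on the remaining 38.

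**How that last coefficient behaves under no treatment effect (illustration).** Let ρ be the ICC and w = (1 − ρ)/5.
- Model-based SE, from within-patient error only: √(2 × 4 × w).
- True SD of the difference between two patients' means: √(2 × 4 × (ρ + w)).
- Ratio k = √(w / (ρ + w)), in which the SD of 2.0 cancels.
- Residual degrees of freedom 200 − 44 = 156, critical value 1.975. Rejection rate ≈ 2 × (1 − Φ(1.975 k)).

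| ρ (assumed) | model SE | true SD | k | rejection, formula | rejection, 4,000 simulations |
|---|---|---|---|---|---|
| 0.3 | 1.06 | 1.88 | 0.564 | 27% | 26% |
| 0.5 | 0.89 | 2.19 | 0.408 | 42% | 42% |
| 0.7 | 0.69 | 2.47 | 0.281 | 58% | 57% |

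A second set of simulations gave 26%, 43% and 58%.

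**After the repair.** With patient as a random intercept, the SE of the group main effect is √[(2/20) × 4 × (ρ + w)] = 0.42, 0.49 and 0.55 VAS points for ρ = 0.3, 0.5 and 0.7.

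**Why group-by-time is also needed.** Suppose, for illustration, no difference at baseline and 2 cm at each of the four later times. A single main effect over all five times then averages to 2 × 4/5 = 1.6 cm. It does not give the effect at separate time points, which the section sets as its aim.

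**The case against.** The strongest reply is that this is a slip of wording. The section names a mixed model and says it handles within-patient correlation, so the authors probably meant patient as the subject unit and put it in the wrong list. Covariance structure is also something an article may leave to the full plan. The first part is likely true. But the article does not leave the matter open: it places patient explicitly among the fixed effects, and nothing elsewhere corrects it. An analyst must depart either from the list or from the description.

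A second reply is that the failure would be noticed. In the order listed, the fit gives a missing coefficient or an error, and someone would correct it before any result existed. This stands, and it limits the weight of the rejection rates. A reader might infer that the trial's longitudinal tests will have 26% to 58% false positives. The documents do not support that. Those figures need an ordinary linear model, group entered before patient, reference coding, an assumed ICC and five time points. VAS also has weekly scores during physiotherapy, and the step-down test is scheduled only at baseline and 12/18 weeks.

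A reader might also infer that the main result is compromised. It is not. The primary regression and the 12/18-week secondary regressions use one value per patient and have no patient term.

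A third reply is that adding group-by-time makes the visit contrasts estimable even with patient fixed. That is correct. The price is precision: each contrast becomes an unadjusted change from baseline, with variance about 2/(1 + ρ) times that of baseline adjustment (ρ here being the correlation between visits), or 1.18 to 1.54 times for ρ from 0.7 to 0.3. The promised main effect would still not be identified.

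**Conclusion.** The point holds for the longitudinal secondary analyses. As written, the model is one rank short and the treatment main effect it promises cannot be estimated. The list of fixed effects also contradicts the section's statement about within-patient correlation. This is an error in what the article states, not a detail left to another document, even if it began as a slip.

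The rank result assumes only that patient is a factor and that each patient keeps one arm. The article says "The primary analyses will be performed following the intention-to-treat method"; reading the longitudinal analyses as randomised too is an assumption, but a natural one. Excluding patients who cross over, as in the per-protocol analysis, also leaves arm constant within patient. The 26% to 58% range only illustrates one software path. Other codings of patient give other arbitrary coefficients, and none gives a valid between-arm test of the main effect. The point should be corrected before analysis; it gives no reason to doubt the design or the primary analysis.

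**What to change.** Reword the model description in the section on secondary endpoints:

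- Remove patient from the fixed effects. Name it as the random-intercept unit, or as the subject of a stated residual covariance across visits.
- Keep categorical time and treatment group as fixed effects and add group-by-time.
- Report between-arm differences at the stated time points, with 95% confidence intervals from standard errors that reflect between-patient variation (for example REML with Kenward-Roger or Satterthwaite degrees of freedom).
- Choose one role for baseline: either an outcome row with baseline as the time reference level, or a covariate with the baseline rows dropped. Using it as both would make it outcome and predictor at once.

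The cost is a few words of analysis text before database lock. It needs no further patients, visits or data. The intervals will be those of a between-patient comparison.
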